## Abstract

**Background:**

Diabetes represents an increasing health burden worldwide. In 2010, the Public Health Department of the canton of Vaud (Switzerland) launched a regional diabetes programme entitled “Programme cantonal Diabète” (PcD), with the objectives to both decrease the incidence of diabetes and improve care for patients with diabetes. The cohort entitled CoDiab-VD emerged from that programme. It specifically aimed at following quality of diabetes care over time, at evaluating the coverage of the PcD within this canton and at assessing the impact of the PcD on care of patients with diabetes.

**Methods/Design:**

The cohort CoDiab-VD is a prospective population-based cohort study. Patients with diabetes were recruited in two waves (autumn 2011 - summer 2012) through community pharmacies. Eligible participants were non-institutionalised adult patients (≥18 years) with diabetes diagnosed for at least one year, residing in the canton of Vaud and coming to a participating pharmacy with a diabetes-related prescription. Women with gestational diabetes, people with obvious cognitive impairment or insufficient command of French were not eligible. Self-reported data collected, included the following primary outcomes: processes-of-care indicators (annual checks) and outcomes of care such as HbA1C, (health-related) quality of life measures (Short Form-12 Health Survey – SF-12, Audit of Diabetes-Dependent Quality of Life 19 – ADDQoL) and Patient Assessment of Chronic Illness Care (PACIC). Data on diabetes, health status, healthcare utilisation, health behaviour, self-management activities and support, knowledge of, or participation to, campaigns/activities proposed by the PcD, and socio-demographics were also obtained. For consenting participants, physicians provided few additional pieces of information about processes and laboratory results.

Participants will be followed once a year, via a mailed self-report questionnaire. The core of the follow-up questionnaires will be similar to the baseline one, with the addition of thematic modules adapting to the development of the PcD. Physicians will be contacted every 2 years.

**Discussion:**

CoDiab-VD will allow obtaining a broad picture of the care of patients with diabetes, as well as their needs regarding their chronic condition. The data will be used to evaluate the PcD and help prioritise targeted actions.

**Trial registration:**

This study is registered with ClinicalTrials.gov, identifier NCT01902043, July 9, 2013.

**Electronic supplementary material:**

The online version of this article (doi:10.1186/s12913-015-0991-0) contains supplementary material, which is available to authorized users.

## Background

Worldwide, chronic diseases constitute a major burden for communities in terms of morbidity, disability and mortality. Their care requires collaboration between healthcare providers, teamwork, training in self-management and the use of evidence based-medicine. However, such care processes are complex and often suboptimal. Thus, chronic disease management (CDM) strategies have been developed as a means of reorganizing healthcare systems and medical treatment for chronic diseases [1–4].

Diabetes is one of the most common chronic diseases, with an estimated number of affected persons of more than 550 million for 2030 [5]. In the canton of Vaud, a Swiss state of ~720.000 residents (approximately 10 % of the Swiss population), a recent population-based study has shown a prevalence of diabetes of about 7 % [6]. In 2010, the Public Health Department of the canton of Vaud initiated the development of a regional programme entitled “Programme cantonal Diabète” (PcD), with both the aim to decrease the prevalence of diabetes in that canton and improve care for patients with diabetes [7]. The political will and support for this innovative programme, at the level of a whole canton, is unique in Switzerland.

Evaluation of CDM programmes is essential to assess their implementation and determine the benefits and effectiveness of their development [8, 9]. Randomized controlled trials (RCT) may not be the most suitable design for evaluating complex interventions such as the PcD, since such interventions are very much context-dependent [10]. In addition, there might be practical difficulties to include control sites, and the resources and costs incurred may be substantial. Moreover, when implemented at a macro level, with no direct inclusion of patients, RCT cannot be considered as an evaluation alternative. Scientifically sound evaluation methods that remain also practical in routine settings are needed; cohort studies may represent such an opportunity.

To assess the impact of the implementation of the PcD on health and care outcomes as well as to obtain a comprehensive picture of patients with diabetes residing in the canton of Vaud, and their care, we opted for a prospective cohort study design. After the baseline data collection, participants will be followed-up annually to assess the evolution of the quality of care over time, the coverage of the PcD within that canton and the impact of the PcD on patients’ care.

## Methods/Design

### Design

The CoDiab-VD is a prospective population-based cohort study launched in 2011 in the canton of Vaud/Switzerland, conducted by the Institute of Social and Preventive Medicine (IUMSP) of the Lausanne University Hospital. Baseline data were collected during a two-wave recruitment period in the autumn of 2011 and in the summer of 2012 (Fig. 1). Patients’ follow-ups will be set up yearly (Fig. 2).

**Fig. 1 Fig1:**
[figure not shown]
Recruitment flowchart ot the CoDiab-VD cohort

**Fig. 2 Fig2:**
[figure not shown]
Study design of the CoDiab-VD cohort

### Study population

#### Sampling frame

Randomly selected community-based pharmacies registered in the canton of Vaud were contacted and asked to participate in the recruitment of patients with diabetes [11]. During a 6 week period, participating pharmacies had to propose the survey to 40 consecutive persons visiting the pharmacy with a prescription for diabetes-related treatment and/or equipment (oral anti-diabetic medications, insulin, glycemic strips or glucose meter). Pharmacists checked patients’ eligibility and briefly described the context and aims of the study. The baseline questionnaire package (information letter, questionnaire, prepaid reply envelope) was given to eligible patients accepting to take it, to complete it at home, and to return it to the investigators by regular mail. Pharmacists did not record contact details of eligible participants because of time and organisation constraints; therefore potentially participating patients with diabetes could not be reminded to send back the questionnaire. For the same reason, the characteristics of non-participants could not be recorded.

### Inclusion criteria

Patients were eligible if they came to a participating pharmacy with a diabetes-related prescription, and were non-institutionalised adults (≥18 years) reporting a diagnosis of diabetes for at least 1 year, residing in the canton of Vaud and able to provide written informed consent.

### Exclusion criteria

Exclusion criteria at baseline were gestational diabetes, obvious cognitive impairment, or insufficient level of French to understand and complete the self-report questionnaire.

### Sample size

The number of patients with diabetes to include in the study was estimated to obtain good precision (i.e. confidence interval width) around the following primary outcomes at baseline: mean HbA1C value, mean Physical and Mental component scores (PCS and MCS) of the Short Form-12 Health Survey (SF-12), mean Patient Assessment of Chronic Illness Care (PACIC) global score, and percentage of patients receiving recommended annual processes-of-care. Considering the clustering of data by pharmacies (40 pharmacies, each recruiting 15 patients, intra-class correlation 0.05, alpha 0.05, beta 0.2), the recruitment of 600 participants was deemed appropriate. This sample size was also large enough to detect a 0.5 % point decrease in HbA1C between two time points. In addition, it was above the sample size required for such a change considering repeated measures within a same individual.

### Baseline measures

#### Patients’ questionnaire

The baseline questionnaire was designed to encompass several aspects of disease, care and life of people living with diabetes. It targeted the following areas: diabetes status, diabetes management and quality of care, health-related quality of life (HRQoL) and quality of life (QoL), health services utilisation, health status and health habits, self-management activities and support, socio-demographics. An overview of all variables collected is shown in Table 1, and a comprehensive description of corresponding questionnaires and answer categories is provided in the Additional file 1.

**Table 1 Tab1:** Overview of the variables, measures and instruments used in the patient self-completed questionnaire

Section	Themes	Instruments, details
Primary outcomes: processes and outcomes quality of care indicators		
Diabetes management	Receipt of recommended processes-of-care	1) Past 12 months: HbA1C check, blood pressure measurement, weight measurement, lipid profile, diabetic foot examination, urine test for microalbuminuria, eye examination by ophtalmologist, influenza vaccination
		2) Anytime: physical activity recommendations, diet recommendations
	HbA1C	Last HbA1C value
Health-related quality of life (HRQoL) and Quality of life (QoL)	Generic HRQoL	SF-12 [15]
	Diabetes-specific QoL	ADDQoL [16]
Patient assessment of chronic care	Congruency of care with the Chronic Care Model (CCM)	PACIC [17, 18]
Exposure variables		
Programme cantonal Diabète^a^	Knowledge of/participation in PcD activities/projects	
Other variables of interest		
Diabetes	Characteristics of the disease	Type of diabetes, disease duration, treatment (drugs)
	Diabetes-related complications	List of following complications: ischemic heart diseases, stroke, retinopathy, chronic kidney disease (CKD) without dialysis, CKD with dialysis or kidney transplant, neuropathy, foot ulcer, lower limb amputation, severe hypo- or hyperglycemia
Diabetes management	Medication adherence	Morisky Medication Adherence Questionnaire [19]
Health services utilisation	Ambulatory care visits, emergency visits, hospitalisation	Utilisation during past 12 months
	Home care services, domestic home support	Received help during past 12 months
	Foregoing care because of costs	Foregoing care during past 12 months
Health status and health habits	Anthropometric values	Weight, height
	Smoking	Smoking status, duration of smoking, smoking products, average number of cigarettes smoked per day, medical advice on smoking cessation
	Alcohol consumption	AUDIT-C questionnaire [20]
	Physical activity levels	Questions from the Swiss Health Survey [21]
	Depression screening	Two validated questions for the screening of depression [22]
	Comorbidities	List of following chronic diseases: heart disease (heart failure, valve disease, heart muscle disease), chronic lung disease (asthma, chronic bronchitis, emphysema), osteoporosis, osteoarthritis or arthritis; cancer or malignancy or lymphoma (with the exception of skin cancer), gastric or duodenal ulcer, depression, Parkinson disease, hypertension, hyperlipidemia, other chronic condition
Self-management activities and support	Home glucose self-monitoring	
	HbA1C knowledge	
	Participation in diabetes education courses	
	Membership in the local diabetes association	
	Knowledge and use of the “Diabetes Passport”^b^	
	“Self-efficacy”	Level of easiness/difficulty to manage diabetes generally, and regarding physical activity, diet, and medication
	Level and source of information about diabetes	
	Support and satisfaction from healthcare team and social network	
	Diabetes care satisfaction and recommandation of their care to others	
Socio-demographics	Characteristics of the participants	Age, gender
	Socio-economic status	Marital status, family size, household income, education, employment, insurance status, place of residence, nationality

*HRQoL* health-related quality of life, *SF-12* short form-12 Health Survey, *ADDQoL* audit of diabetes-dependent quality of life 19, *CCM* chronic care model, *PACIC* patient assessment of chronic illness care

^a^Since the 2012 recruitment

^b^A small booklet with data, information and reminders

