#### Primary outcomes: processes and outcomes quality of care indicators

We considered as primary outcomes all usually recommended diabetes processes-of-care indicators, as well as the following outcomes of care indicators: HbA1C levels, as an intermediary outcome associated with future development of diabetes complications [12–14], HRQoL and QoL as measured using a generic tool (SF-12) [15] and a diabetes-specific quality of life tool (Audit of Diabetes-Dependent Quality of Life 19 – ADDQoL) [16], respectively, and patient assessment of chronic care, i.e. how care is congruent with the Chronic Care Model (PACIC) [17, 18].

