### Follow-up

#### Follow-up process

Participants will be followed annually by mail questionnaires (information letter, paper questionnaire and prepaid reply envelope). To maximise retention of participants in the cohort, we will send a postcard reminder 2 weeks after the first mailing to non-respondents and a complete reminder package again 2 weeks later (questionnaire, information letter and prepaid reply envelope). Persistent non-respondents will be contacted by telephone; a minimum of three contact attempts over different days and times is planned.

Because of time constraints and overall limited participation to research projects, treating physicians will be contacted every 2 years only.

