### Follow-up questionnaires

The core of the follow-up patients’ questionnaires will be similar to the baseline questionnaire, particularly with regard to the questions targeting primary outcomes, healthcare utilisation, health status and health habits as well as to the questions assessing knowledge and participation to PcD projects. According to the needs and specific interests of the PcD, new questions or thematic modules will be added to the follow-up questionnaires. In 2013 for example, a module on diabetic foot, as well as the Stanford self efficacy questionnaire and a health literacy question were added. In order to keep a questionnaire of a reasonable length, questions representing variables other than primary outcomes may be removed momentarily from the follow-up questionnaire.

The physicians’ questionnaire will be similar to the baseline one.

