The cohort CoDiab-VD is, however, subject to several limitations. First, the number of patients recruited was below the sample size calculated (inclusion of 519 participants instead of the planed 600). However, because of a greater number of clusters (pharmacies) than expected and a conservative sample size calculation, the precision around point estimates was nevertheless acceptable. This sample size is also large enough (power > 90 %) to detect a 0.5 % point decrease in HbA1C, a PCS or MCS change of 5 points, a PACIC change of 0.3, or an absolute change of process of care of 10 %. Second, one could criticize the choice of self-reported data for the majority of the outcomes, since they may be prone to recall bias – an inherent limitation of such data collection, or be over- or underestimated. Specific analyses, on a fraction of the cohort data, demonstrated a good agreement between patient- and physician-reported outcomes for simple processes-of-care, such as measurement of blood pressure, HbA1C, weight and lipid profile [27]. Physician-reported outcomes were asked for in a second phase. Since their collection was dependent on the physicians’ willingness to participate, these variables were only available for a fraction of the sample, about 50 % at both recruitments and first follow-up. We will nevertheless favour the collection of some physician-reported measures (i.e. blood pressure, HbA1C value) in the future because they are more accurate. Third, between the 2011 baseline recruitment and their first follow-up in 2012, 58 patients refused to continue to participate in the cohort, what could be explained by the lack of information of the 2011 initial group of patients about the annual follow-ups to come. Globally however, when considering patients both recruited in 2011 and in 2012, this amounted to only a tenth of the total baseline sample size. In addition, the comparison of characteristics of participants to the baseline and of participants to the 2013 follow-up did not highlight major differences.

CoDiab-VD will allow drawing a broad picture of patients with diabetes and their care over time. It will also contribute to the evaluation of the PcD and to support decisions about which targeted actions to implement.

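### Influenza vaccination, a primary indicator, is asked over a rolling 12 months in an autumn and a summer wave, so the waves can cover different vaccination seasons and the autumn wave can read too low

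*Protocol article*

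**What the plan says.** Table 1 (Baseline measures, Patients' questionnaire) lists ten process-of-care items. Two are asked as ever received. Eight share one recall window, which opens "Past 12 months: HbA1C check, blood pressure measurement, weight measurement" and closes "urine test for microalbuminuria, eye examination by ophtalmologist, influenza vaccination". The section on primary outcomes gives them all primary status: "We considered as primary outcomes all usually recommended diabetes processes-of-care indicators".

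On timing, the Design section states: "Baseline data were collected during a two-wave recruitment period in the autumn of 2011 and in the summer of 2012". Within a wave, the Sampling frame section states: "During a 6 week period, participating pharmacies had to propose the survey to 40 consecutive persons". Patients completed the questionnaire at home and could not be reminded, so the completion date was not controlled.

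The primary-outcome questions are kept at follow-up, which is yearly: "Participants will be followed annually by mail questionnaires". The text gives no calendar month for any follow-up. Physicians are asked for the date of influenza vaccination, but their data exist for about half the sample, and they are contacted only every 2 years.

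The Discussion names a 10-point absolute change in a process of care as detectable with power above 90%.

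**The concern.** For a blood pressure or HbA1C check, any 12-month window is much like another. A seasonal vaccination is different, because what the window contains depends on where in the campaign it is cut. In summer the cut falls between campaigns and the window holds one complete season. In autumn it may fall inside a campaign. The same question then measures receipt in one identifiable season for one wave, and receipt in pieces of two seasons for the other.

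The cohort exists to follow quality of care over time. If influenza vaccination is pooled over the two waves, or the waves are set side by side, part of any difference may come from the calendar and not from care. The answers alone do not show which season a yes referred to, so this has to be handled mainly when the question is asked.

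**Working it through.** **Benchmark.** The article states power above 90% for a 10-point change with 519 participants. It gives no base rate, so I assume 50% rising to 60%, with 519 at each time point and no design effect. The standard error is √[(0.50×0.50 + 0.60×0.40)/519] = √(0.49/519) = 0.0307. Then 0.10/0.0307 − 1.96 = 1.29, and power is about 0.90. The figure reproduces and is not disputed; 10 points serves only as the yardstick.

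**Assumption not in the document.** Influenza vaccination is given mainly in autumn to early winter.

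**What each window contains.**
- Summer 2012: the whole 2011/12 campaign.
- Autumn 2011, before the campaign: the whole 2010/11 campaign.
- Autumn 2011, during the campaign: the late part of 2010/11 plus the early part of 2011/12.

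**One person.** Vaccinated on 25 October 2010 and 10 November 2011, answering on 1 November 2011. The window starts on 1 November 2010. The first vaccination is seven days too early and the second has not yet happened. The correct answer is no, although the person is vaccinated every season.

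**General form.** Let p be uptake per season (constant), s the share who start and also the share who stop between the two seasons, and F the fraction of a campaign's vaccinations already given by the answer date.

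*Same personal date every year.* Persistent vaccinees contribute p − s, starters F·s, stoppers (1 − F)·s. The sum is p − s + F·s + (1 − F)·s = p. The artefact is 0 at any F.

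*Dates independent between years.* A persistent vaccinee is missed when the first vaccination fell too early (probability F) and the second is still to come (probability 1 − F). The sum is (p − s)[1 − F(1 − F)] + F·s + (1 − F)·s = p − (p − s)·F(1 − F). The autumn wave is therefore lower by (p − s)·F(1 − F).

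Two cases:
- A, same people every season (s = 0): deficit p·F(1 − F).
- B, uptake also independent between years (s = p(1 − p)): deficit p²·F(1 − F).

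Deficit of the autumn wave in percentage points, for assumed p:

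| p | A, F = 0.25 or 0.75 | A, F = 0.5 | B, F = 0.25 or 0.75 | B, F = 0.5 |
|---|---|---|---|---|
| 0.40 | 7.50 | 10.0 | 3.00 | 4.00 |
| 0.50 | 9.38 | 12.5 | 4.69 | 6.25 |
| 0.60 | 11.25 | 15.0 | 6.75 | 9.00 |
| 0.70 | 13.13 | 17.5 | 9.19 | 12.25 |

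At F = 0 or F = 1 the deficit is 0. A summer answer always gives p.

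**True change between seasons.** If uptake really rises by 5 points from 2010/11 to 2011/12 and personal timing is stable, the summer wave reads p + 0.05 and the autumn wave p + 0.05F. The gap is 5(1 − F), or 0 to 5 points. This is a real season difference, but in the data it appears as a wave difference.

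**The case against.** The strongest objection is that every 12-month window offers exactly one year of opportunity. With stable uptake and stable personal dates nothing is distorted. The text does not say in which weeks of autumn 2011 patients answered; if that was before or after the campaign, each window holds one whole season. This stands: the artefact is possible, not demonstrated, and its upper range needs dates that vary independently from year to year, which is an extreme case.

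Table 1 is an overview, and the full item wording is in Additional file 1, which is not shown. A season might be named there, though Table 1 gives only the 12-month window. Physician dates would allow a check, but only in about half the sample.

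Some stronger readings are tempting and are not supported:

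- A reader might infer that an autumn window counts anyone vaccinated in either of two campaigns and so inflates coverage by the share of new vaccinees, say 5 to 10 points. That describes a 24-month window. A 12-month window never holds two full campaigns, and with constant uptake the artefact above is zero or a deficit.
- A reader might infer from the mention of a 2013 follow-up that both waves share one mailing, so that at least one is followed in another season than its baseline. The text gives years only, as in "between the 2011 baseline recruitment and their first follow-up in 2012, 58 patients refused to continue", and the design figure is not shown. If each wave is followed in its own season, the cut stays at the same point of the campaign within a wave.
- A reader might infer that wave is used to judge the effect of the cantonal programme on vaccination. The programme questions were added in 2012 to describe differences in exposure and awareness; no outcome contrast between waves is stated.
- Nothing here calls for wave or month terms in the analysis of the other primary outcomes.

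**Conclusion.** The point holds as a measurement weakness in one of ten process-of-care items. Given mainly autumn to early-winter vaccination, the rolling window does not refer to the same season in both waves and can miss people vaccinated in both seasons if they answered during the campaign.

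Its size cannot be settled from the document. With constant uptake it runs from 0 to a deficit in the autumn wave of up to about 4 to 12 points (case B) or 10 to 17.5 points (case A), both at half the campaign elapsed and uptake of 40 to 70%. These are upper ends under stated assumptions, not estimates. Because they straddle the article's 10-point benchmark, the matter deserves a remedy. The pooled baseline is affected only in proportion to the autumn wave's share, which the text does not give.

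A baseline-to-follow-up artefact arises only if a wave's follow-up falls in another season than its baseline. The sample size is not touched.

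**What to change.** From the next questionnaire, add one item asking whether the participant was vaccinated against influenza in the last completed autumn/winter season, naming the years. Keep the 12-month item beside it so that comparability with baseline is preserved. The plan already allows additions of this kind: "In 2013 for example, a module on diabetic foot" is one it reports.

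Report the influenza data already collected by wave and not only pooled, stating which campaign each window can cover. Record the completion date of each questionnaire, if this is not already done. Where physicians supplied a vaccination date, use it to check in that subset how often the 12-month answer and the named season disagree.

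The cost is one extra question and one date field. The named-season series starts only when the item is introduced, so the autumn 2011 baseline stays ambiguous except where a physician date exists.
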